### Correlation analysis

We will run correlations matrix between CORSI, SBSOD, and hits at both the VSCT and SCT. This will help us understand the influence of general intelligence and working memory capacity on spatial ability and ensure that the VSCT and SCT are comparable tasks

Regarding reliability, we plan to assess internal consistency using split-half and/or Cronbach’s alpha methods for key performance metrics (e.g., accuracy, error scores), depending on distributional characteristics. In addition, we aim to conduct a test–retest reliability study in a subsample of participants to examine stability over time.

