### Participants

As the study aims to evaluate
**convergent and discriminant validity** of VSCT, by comparing VSCT correlation with SCT to the correlation of RAVLT with SCT, an
*a priori* power analysis was conducted using

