**G*Power 3.1**
Faul *et al.* (2009). Assuming a
**moderate to large effect size (Cohen’s q = 0.4)**, a significance level of
**α = 0.05**, and a desired power of
**0.95**, The required sample size for comparing two independent correlation coefficients using a z-test for dependent Pearson’s r was calculated as 166
**participants**. Taken this for granted, and bearing in mind that the data to correlate are not yielded with a paper-and-pencil questionnaire- but a virtual setting requiring training and adaptation, we weight the effect size indication with previous research using similar aims and methods.

This was the case in
da Costa *et al.* (2022), who validated two immersive virtual reality tasks for spatial orientation using correlational and group comparison analyses. The authors reported significant associations between the virtual tasks and traditional cognitive measures, as well as successful group discrimination.

The participants represented a sample size large enough to yield statistically reliable confidence intervals. It should be noted that the study employed a between-subjects design; however, participants from the two groups were combined. In contrast, our study will correlate the two groups with two different variables.

Furthermore,
*
He *et al.* (2022)
* employed a fully within-subjects design to validate a spatial perspective-taking task in ambulatory virtual reality, using a sample size comparable to ours. However, since within-subjects designs typically offer greater statistical power, we acknowledge that our between-subjects design may require a larger sample to achieve equivalent sensitivity. We have accounted for this by adopting a conservative effect size estimate and grounding our decision in the specific demands of VR-based testing, which introduces variability due to training and adaptation phases.

Participants will be actively recruited to participate in the intervention across various University of Bologna Campus locations. Recruitment will be facilitated through targeted advertisements and consecutive enrollment procedures to ensure diverse participant representation and data robustness. 

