*Procedure*
**

 Participants will be assigned in a pseudo-randomized single-blinded manner to one of the two groups (Auditory Verbal (AV) vs. Virtual Reality (VR)). Both groups will be asked to perform an initial assessment of their spatial abilities using the 40-item version of SCT. In the next phase, the experimental group will be made to wear the "HTC VIVE" visor that will allow them to perform the Virtual Spatial Configuration Task in VR (VR condition); the control group will be administered the auditory verbal memory task (AV condition). Both groups will be given the SCT again at the end of the task (See
Figure 2). 

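### The Plan of analysis omits the correlation comparison that sets the sample size and makes no use of the RAVLT; the alternative VSCT–RAVLT correlation cannot be computed in this design

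*Protocol article*

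**What the plan says.** **Aim and sample size.** Under Participants, the article says it will evaluate convergent and discriminant validity "by comparing VSCT correlation with SCT to the correlation of RAVLT with SCT". The power calculation follows: Cohen's q = 0.4, alpha 0.05, power 0.95. The result is given as "The required sample size for comparing two independent correlation coefficients using a z-test for dependent Pearson’s r was calculated as 166" participants. The same section adds that "our study will correlate the two groups with two different variables".

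**Role of the RAVLT.** The Introduction (Validation of a new 3D spatial task) says the RAVLT is there specifically for discriminant validity. It expects no significant VSCT–RAVLT correlation and treats that absence as the evidence.

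**Who takes what.** Under Procedure, "Participants will be assigned in a pseudo-randomized single-blinded manner to one of the two groups". Both groups take the SCT before and after the task. Between the two, the VR group does the VSCT and the control (AV) group does the RAVLT.

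**Planned analyses.** The Plan of analysis contains:
- t-tests between groups on SCT hits, and on Corsi and SBSOD scores to check equivalence;
- a correlation matrix: "We will run correlations matrix between CORSI, SBSOD, and hits at both the VSCT and SCT";
- internal consistency and test–retest reliability.

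Of the matrix it says: "This will help us understand the influence of general intelligence and working memory capacity on spatial ability". Expected results mentions neither the RAVLT nor discriminant validity.

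**The concern.** The question that fixes the number of participants has no counterpart in the section that says what will be done with their data. The matrix names its four variables, so the RAVLT is absent from an explicit list; this is not a general statement that happens to be short.

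A team following that section would collect RAVLT scores in a whole arm, leave them out of every listed analysis, and not run the test the study was sized for. The likely alternative is that the comparison is added once data are in. The RAVLT yields several scores (immediate trials, post-interference, delayed recall, recognition), and none is named for the comparison. The choice of score and of test would then be open when the results are already visible, and the discriminant claim would rest on that choice.

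**Working it through.** **1. Does any listed analysis address discriminant validity?**

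| Source | Quantity needed | In the Plan of analysis? | Computable under Procedure? |
|---|---|---|---|
| Participants | r(VSCT, SCT) against r(RAVLT, SCT) | First correlation is a matrix cell; the second, and the comparison, are not listed | Yes, between groups |
| Introduction | r(VSCT, RAVLT) | No | No: no participant takes both tasks |

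The between-group comparison is therefore the only one of the two that the design allows, and it is not in the plan. Adding the RAVLT as another row of the matrix would not repair this. Its VSCT cell would be empty, and a matrix does not test a difference between two correlations.

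**2. Reproducing the sample size.**

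Inputs from Participants: q = 0.4, alpha = 0.05, power = 0.95. Sidedness and allocation ratio are not stated; I take 1:1 and show both sides.

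For two independent correlations, n per group = 2 × [(z for alpha + z for power) / q]² + 3.

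- Two-sided: 2 × [(1.960 + 1.645) / 0.4]² + 3 = 165.4, so **166 per group, 332 in total**.
- One-sided: 138.3, so 139 per group, 278 in total.

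The article's 166 is thus the per-group figure of the two-sided test for independent correlations.

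The article also calls the test dependent. For dependent correlations sharing the SCT, the total depends on a third correlation, VSCT with RAVLT, which the article does not give. Assuming correlations of 0.38 and 0 (q = 0.4), the two-sided total is 166, 133, 117 or 85 for a third correlation of 0, 0.2, 0.3 or 0.5. So 166 can also arise as a total, but only if everyone takes both tasks, which Procedure rules out.

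**3. Power of the missing test.**

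Two-sided power = Φ( q / √(2/(n − 3)) − 1.960 ).

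- n = 166 per group: 0.4 / √(2/163) = 3.611; 3.611 − 1.960 = 1.651; power **95.1%**.
- n = 83 per group (166 in total): 0.4 / √(2/80) = 2.530; 2.530 − 1.960 = 0.570; power **71.6%** (81.2% one-sided).
- Difference detectable with 95% power at 83 per group: (1.960 + 1.645) × √(2/80), giving q = 0.57.

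**4. Would a non-significant correlation be enough?**

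Even if both tasks were taken by 83 people and the observed r were 0, the 95% interval would be tanh(±1.96/√80) = ±0.22. That is compatible with a modest association in either direction, so non-significance alone is weak evidence of distinctness.

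**The case against.** The strongest reply is that the intent is on the page. Participants names the comparison as the aim and mentions a z-test for it, and the Introduction states the discriminant hypothesis and how it would be judged. A journal article condenses a fuller protocol, which may carry the detail.

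Part of this stands. A reader might infer that the article nowhere contemplates a discriminant test; it does, and the fault is that the aim and sizing are not carried into the planned analyses. But the article has its own Plan of analysis with an explicit variable list, so this is a disagreement between two sections of one document. Nor can the sizing sentence serve as the specification, since it calls the same test both independent and dependent.

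Four further inferences go beyond the text:
- That only convergent correlations could be reported. Group t-tests and reliability analyses are also planned, and the AV task doubles as the non-spatial comparison condition.
- That the study will draw a conclusion about intelligence. No hypothesis or expected result concerns it; the mention of general intelligence is a wording slip.
- That unequal numbers across matrix cells are an error. That is usual in a pairwise matrix and is a matter of presentation.
- That the study is certainly underpowered. The shortfall applies if 166 is the total, which is the natural reading of the article but is not settled by it.

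**Conclusion.** The point holds as an internal contradiction. Discriminant validity is a stated aim and its comparison sets the sample size, yet the Plan of analysis neither lists that comparison nor uses the RAVLT. The Introduction's substitute, a VSCT–RAVLT correlation, cannot be estimated because no participant takes both tasks.

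These conclusions rest on the text alone. The power figures rest on q = 0.4, a two-sided 5% test and 1:1 allocation: 95% power takes 166 per group, and 166 in total gives about 72%.

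This should be settled before data are analysed, because the article's discriminant claim depends on it.

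**What to change.** 1. **Add the test to the Plan of analysis.** A two-sided Fisher z test for independent correlations: r(VSCT, SCT at T1) in the VR group against r(RAVLT, SCT at T1) in the AV group, reported as q with a 95% confidence interval. SCT at T1 is what the Introduction already reserves for correlations with the VSCT.
2. **Fix one RAVLT score in advance.** The total of trials 1–5 is one reasonable choice; what matters is that it is named beforehand.
3. **Withdraw the VSCT–RAVLT hypothesis or restate it** as this between-group comparison, and limit the claim. The comparison shows whether the SCT relates more strongly to the VSCT than to verbal memory; it gives no direct estimate of how the VSCT relates to verbal memory. Such an estimate would need both tasks in the same people, which is a design change.
4. **Restate the power.** Describe the test as one of independent correlations, give sidedness and allocation, and say whether 166 is per group or in total. If it is the total, either report about 72% power at q = 0.4 or plan for 332.
5. **Minor:** remove the reference to general intelligence under Correlation analysis, since no listed instrument is described as measuring it.

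Items 1–3 and 5 cost wording and a few lines of code. Item 4 costs only wording if the lower power is accepted. Keeping 95% power would double recruitment from 166 to 332.

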We will use a series of tests and tasks to validate the VSCT. We hypothesize a positive correlation between the VSCT and SCT, as both are designed to measure the same construct—namely, the ability to form cognitive maps. We also hypothesize a positive correlation between the VSCT and Backward Corsi, as working memory is a key component in the formation and maintenance of cognitive maps (
Epstein *et al.*, 2017). Conversely, we do not expect a significant correlation between the VSCT and RAVLT. We included the Rey Auditory Verbal Learning Test (RAVLT) in our study precisely to assess discriminant validity. The RAVLT measures verbal episodic memory, while the VSCT targets visuospatial configuration memory—two constructs that are theoretically and empirically distinct (
Suri *et al.*, 2017). By including the RAVLT and confirming that it does not significantly correlate with performance on the VSCT, we provide evidence that the VSCT is not simply capturing general memory ability, but rather a more specific visuospatial memory component. This lack of correlation supports the discriminant validity of our task, helping to confirm that it measures a construct different from that assessed by standard verbal memory tasks.

Finally, to evaluate VSCT feasibility we will use the Simulator Sickness Questionnaire (SSQ) (
Kennedy *et al*., 1993).

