**Figure 1. f1:**
[figure not shown]
**a.** Main menu interface presented at the beginning of each scene, allowing participants to change scenes, return to the home screen, or exit the task.
**b.** Example view of the full environment, showing all five objects placed in a triangular configuration. This layout illustrates the type of spatial arrangement participants are required to learn.
**c.** At the start of each trial, only the two front objects are visible to the participant, who must respond to a question about the missing (third) object based on memory. A floor circle indicates the location of the hidden object.
**d.** If the participant selects the wrong answer, the environment allows them to rotate and discover the third object's location. This feedback mechanism supports gradual learning of the spatial configuration.

The location of the missing object was indicated by a circle on the floor (
Figure 1c/d), providing a visual landmark to aid participants. An interactive interface allowed participants to switch scenes by pressing "change", return to the main menu with "VSCT", and exit by pressing "exit" (
Figure 1a). Participants could explore objects around them for a maximum of 20 seconds per scene.

From the beginning of the task, participants were prompted with questions about the spatial location of objects. Each scene included a canvas displaying a question (e.g., "Which object is behind you?") with three possible choices representing the missing object. Only the two adjacent objects in front of the participant were shown (
Figure 1b). Button positions were randomized to avoid spatial response biases. Participants learned the correct answers through trial and error, gradually forming internal representations of the spatial configurations based on feedback. The task consisted of 40 such trials. For each trial, the participant’s response was recorded.

**
*Environment exploration*
**

Participants could rotate and inspect the environment by moving right or left, using the Unity Interaction Toolkit and custom scripts to interface with the HMD joysticks. Users’ movements are continuous and based on the participant's head direction to ensure ecological validity with proprioceptive feedback and reduce motion sickness.

**
*Data repository*
**

At the end of the project, the project source code will be published in a dedicated public repository on Git Hub to encourage further development and research (
https://github.com/[name]/VSCT). 

**

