**Figure 2. f2:**
[figure not shown]
Figure depicting the timelie of the experimental procedure.

**
*VR spatial task condition*
**

 Training: The participants will be placed in our virtual environment and instructed to explore the space around them in each of the scenes. In each scene, the participant will see 3 objects at a time (two in front of him and one behind him).

Testing: After the training is completed, participants will be asked to start the testing phase. This phase will last until the task is completed, namely, when the participant accurately recalls the position of the objects after three consecutive correct trials. The objects are those learned during the training phase. The participants' accuracy and reaction time will be recorded.

**
*AV memory task condition*
**

Administration of the RAVLT will involve several steps:

The experimenter will read the first list (List A) of 15 unrelated words at a rate of about one word per second. It's crucial to present the words in the same order and with the same pronunciation for each participant. After presenting the list, the participant will be asked to repeat back as many words as they can remember, regardless of the order. After the participant recalled as many words as possible from List A, the process will be repeated for five immediate recall trials. After each trial, the number of words correctly recalled will be recorded. 

The experimenter will read a second list (List A) of 15 unrelated words (List B) to the participant and instruct them to recall as many words as possible from this list. This step is designed to interfere with the participant's ability to recall words from List A. Following the presentation of List B, the participant will be asked to recall the words from List A once again. This step assesses the individual's ability to retrieve information from memory after interference.

After a short delay in which the participant will have to do a scrambled image test (usually around 20–30 minutes), the participant will be asked to recall the words from List A once more without presenting the word list again. This step evaluates the individual's ability to retain information in memory over time.

The participant's performance will be scored based on the number of words correctly recalled or recognized during each test phase.

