### Expected results

**
*Validation of VSCT outcomes*
**

We expect SCT mean accuracy to be positively correlated with performance on the CORSI backward task and VSCT accuracy.

A positive correlation with SCT accuracy would validate VSCT as a measure of participants' abilities to maintain and retrieve cognitive maps based on allocentric frameworks (
Burles *et al*., 2017). Both SCT and VSCT require creating an allocentric cognitive map from multiple egocentric viewpoints. Therefore, we expect a positive correlation between SCT mean accuracy and spatial working memory, as measured by the Corsi backward task. Regarding reliability, based on our planned analyses, we expect to find acceptable to high internal consistency for key performance metrics (e.g., accuracy, error scores), as assessed through split-half reliability and/or Cronbach’s alpha, depending on the distributional properties of the data. Additionally, we anticipate that test–retest reliability in a subsample will demonstrate moderate to high stability over time, supporting the robustness of both the SCT and VSCT as reliable tools for assessing spatial cognition.

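### The VSCT's test length (40 trials or stop at three correct in a row) and its score (hits or accuracy) are not reconciled; on one reading the validating correlation changes sign

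*Protocol article*

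**What the plan says.** Four parts of the protocol article bear on how the VSCT is run and scored.

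- **Number of trials.** The virtual task section describes three-choice questions ("with three possible choices representing the missing object") and states: "The task consisted of 40 such trials". It does not say whether these are training trials, test trials or both.
- **End of testing.** Procedure, VR spatial task condition, says when testing ends: "This phase will last until the task is completed, namely, when the participant accurately recalls the position of the objects after three consecutive correct trials". It gives no maximum. Scene setup assigns five scenes to testing, but nothing says whether the criterion applies once or in each scene.
- **Score.** The same Procedure text says: "The participants' accuracy and reaction time will be recorded". Correlation analysis instead names hits: "We will run correlations matrix between CORSI, SBSOD, and hits at both the VSCT and SCT". Expected results returns to accuracy: "We expect SCT mean accuracy to be positively correlated with performance on the CORSI backward task and VSCT accuracy".
- **Direction that counts as validation.** The introduction says: "We hypothesize a positive correlation between the VSCT and SCT, as both are designed to measure the same construct". Expected results treats a positive correlation with SCT accuracy as what would validate the VSCT.

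Correlation analysis also plans split-half and/or Cronbach's alpha for the key performance metrics. The SCT is the 40-item version.

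**The concern.** With a fixed number of trials, hits and accuracy rank participants identically, so it does not matter which word is used. Under a rule that stops at three correct in a row, they come apart. A participant who is always right stops with three hits. A participant who errs must continue, and keeps adding correct answers on the way to the criterion. The raw count then falls as ability rises, while the proportion correct rises.

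The VSCT-SCT correlation is the article's main evidence of convergent validity. If the sign depends on an unstated choice of test length and score, a sound task could be judged invalid, or the score could end up being chosen after the data are seen. Trials that were not administered cannot be recovered afterwards.

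**Working it through.** The plan gives no figure for VSCT hits to reproduce, and its sample size of 166 does not enter this point.

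**Inputs from the article:** stop at three consecutive correct trials; 40 trials; three choices, so a guessing rate of 1/3; a 40-item SCT; five test scenes.

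**Step 1: expected hits at stopping.** Let p be a constant probability of a correct answer. The mean number of trials to three correct in a row is E[N] = (1 - p³) / ((1 - p)p³) = (1 + p + p²)/p³. By Wald's identity, E[hits] = p × E[N] = (1 + p + p²)/p². For example, p = 0.5 gives 1.75/0.25 = 7.0. If 40 is read as a cap, E[hits] = p × E[min(N, 40)]. The capped mean number of trials is 25.82 at p = 1/3 and 13.50 at p = 0.5.

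| p | Hits, stop rule, no cap | Hits, stop rule, cap 40 | Hits, 40 fixed trials |
|---|---|---|---|
| 1/3 | 13.0 | 8.6 | 13.3 |
| 0.5 | 7.0 | 6.75 | 20 |
| 0.7 | 4.5 | 4.5 | 28 |
| 0.9 | 3.35 | 3.35 | 36 |
| 1 | 3.0 | 3.0 | 40 |

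Under the stop rule the count falls steadily with ability, with or without the cap. With 40 fixed trials it rises.

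**Step 2: correlation with the SCT.** This step needs assumptions that the article does not supply:

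- VSCT and SCT abilities are bivariate normal with latent correlation 0.5, 0.7 or 1.0.
- p = 1/3 + (2/3) × logistic(location + ability) for both tasks, with ability SD 1 and location 0, 0.8 or 1.6, giving a mean p of about 0.67, 0.77 or 0.85.
- Each run is capped at 40 trials, with 200,000 virtual participants per setting.

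Ranges are over the three difficulty levels.

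| Latent r | 40 fixed, hits | One run, hits | One run, proportion | Five scenes, hits | Five scenes, proportion |
|---|---|---|---|---|---|
| 0.5 | 0.37 to 0.40 | -0.17 to -0.19 | 0.22 to 0.25 | -0.29 to -0.32 | 0.34 to 0.38 |
| 0.7 | 0.53 to 0.55 | -0.25 to -0.27 | 0.31 to 0.35 | -0.42 to -0.45 | 0.49 to 0.54 |
| 1.0 | 0.78 to 0.80 | -0.37 to -0.39 | 0.45 to 0.51 | -0.63 to -0.65 | 0.72 to 0.78 |

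A separate model in which p rises over trials gave -0.25 for hits and +0.21 for proportion correct after one run, against +0.53 for 40 fixed trials.

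**Step 3: compression and item sets.** With one run, 46% to 74% of simulated participants score exactly three hits, and about 33% to 67% stop after exactly three trials. Participants who stop at different points have not answered a common set of items, so trial-level alpha or split-half has no complete item matrix. Three trials, all correct, cannot usefully be split.

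**The case against.** The strongest reply is that the article never says the stop rule overrides the 40 trials, nor that hits is an unadjusted count. For the fixed-length SCT it uses number of hits (t-test section) and mean accuracy (Expected results) interchangeably, so it may do the same for the VSCT. Accuracy is the score recorded in the Procedure and the one named in the expectation. With 40 fixed trials, or with accuracy as a proportion, the correlation keeps its positive sign. If the criterion applies in each of five scenes, proportion correct also loses little against 40 fixed trials. The 40 trials might instead be the learning trials that The virtual task section describes, with the criterion governing only the test.

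Most of this stands. A reader might infer that VSCT testing certainly ends after three correct answers and that the planned correlation must therefore be negative. The documents do not support that: it requires both the stop rule and a raw count, and the article fixes neither against its own contrary statements.

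The reply does not remove the inconsistency. The Procedure is the only place that says when testing ends, and Correlation analysis is the only place that names the score for the matrix. Followed literally together, they give the reversed sign. Treating 40 as a cap does not help, and applying the criterion in each scene strengthens the reversal for raw hits. This is also not detail left to a fuller document, because these are statements in the article that do not fit together.

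**Conclusion.** The point holds as an internal inconsistency with a serious conditional consequence.

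- **Stop rule with raw hits:** a valid task would correlate negatively with the SCT, at about -0.2 to -0.4 for one run and -0.3 to -0.65 over five scenes.
- **Stop rule with proportion correct:** the sign is right. A single run gives about 0.2 to 0.5 where 40 fixed trials give about 0.4 to 0.8; over five scenes most of that loss disappears. The problem with trial-level alpha and split-half remains.
- **40 fixed test trials:** hits and accuracy are equivalent and the plan works.

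The fall of expected hits with ability is exact for constant p. The sizes of the correlations rest on the assumed ability distributions and latent correlations, but the negative sign for raw hits appeared in every setting tried. The conflict should be resolved before VSCT data are collected.

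**What to change.** Reconcile The virtual task section with the testing paragraph of the Procedure. State whether the 40 trials are training or test trials, and whether three in a row applies once or per scene. Define one VSCT score and use the same name in Correlation analysis and Expected results.

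The preferred form is to give every VR participant the same 40 scored test trials and score hits out of 40, in parallel with the 40-item SCT. Three in a row can then serve to end training, or be reported as a descriptive measure.

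If the stop rule stays for testing, do not correlate raw hits. Use proportion correct, or trials to criterion with the sign reversed (unreversed, it correlates at about -0.20 to -0.45 with the SCT for one run). Drop trial-level alpha and split-half for the VSCT.

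The cost is wording and one task setting, with no extra participants. The preferred form adds headset time for fast learners: up to 37 more trials (40 - 3) for someone who would have stopped at three. That is worth noting because simulator sickness is the feasibility measure.
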